## Discussion

We expect to find positive treatment effects in all intervention groups for all outcomes in comparison with the usual care or control group. Furthermore, we expect to demonstrate the additive effects of acupuncture and MTT as a combination treatment and to provide scientific evidence to support the implementation of this complex health intervention. Since the two interventions differ in their mechanisms of action, consequently they exert analgesic, autonomic, and psychological effects at different levels. Thus, we expect different effects for each group for pain, the primary endpoint, and for the various secondary endpoints, such as mood, psychological stress, quality of life, and frequency of pain episodes. In addition, we believe that analyzing the correlations between the various outcome parameters with the applied treatment will provide information about the levels at which the effects occur. Furthermore, the influence of temporomandibular disorder on treatment effects will be a basic component of the data analysis. Figure 3 shows how the outcomes are related to each other. An evaluation of adverse events and their severity are important for safety and for patient acceptance of the treatment. Finally, these treatment modalities will be rated by the participating patients with regard to content and time requirements.

**Fig. 3 Fig3:**
[figure not shown]
How the outcomes are related to each other. TCM traditional Chinese medicine

The innovative diagnostic tools (pain mapping and a video analysis of pain gestures) used in the study will provide further valuable outcomes due to their relevance and the additional information. A positive correlation between the patient’s pain mapping and the independent TCM diagnosis, which focuses on the meridians affected, will bring an improved and objective TCM diagnosis to everyday clinical practice. The same applies to pain gesture analysis, which has so far received insufficient attention, even though it broadens the possibilities for differential diagnoses of headaches and may have a decisive role by informing treatment decisions. A tongue diagnosis and its inter-rater reliability will also be addressed in the analysis.

A dedicated research outpatient clinic for integrative Chinese medicine was established for this study with the support of the China Academy of Chinese Medical Sciences. Thus, the proposed research project will also offer the opportunity to evaluate the feasibility of integrating such an outpatient clinic into the day-to-day operations of a medical university.

The main results for the primary outcomes are expected to be offered to the journal *Cephalalgia* as an alternative to the journal *Headache* for publication. The complementary aspects will be disseminated as follows. HRV results will be offered to *Autonomic Neuroscience*, TMD results to *Journal of Oral Rehabilitation*, and pain body gesture results to *Complementary and Alternative Medicine*. Oral and poster presentations will be made in international congresses. Extracts from the results of the study will be made accessible to the public, after their publication in journals, on the homepage of the clinic and in newsletters, as well as the print and online media of the Hannover Medical School press office (for example MHH Info, research reports, and information for patients and doctors).

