In addition, the study will assess whether those participating in the study have a functional disorder of the chewing system (temporomandibular disorder or TMD). Speciali and Dach [12] considered several epidemiological studies in a systematic review, which showed the co-occurrence of TMD and tension-type headaches. Moreover, published studies have shown improvements in headaches when a co-existing TMD was treated with dental interventions alone [13].

By involving experts in TCM, the proposed study may provide information about another interesting aspect, which is that tension-type headaches are described as a mild to moderate, holocranial headaches with a dull, pressing character [14]. However, differences in the location of maximum pain have no impact on treatment decisions based on the International Classification of Headache Disorders (3rd Edition) [15] of the International Headache Society (IHS). By contrast, the acupuncture points to be used for treatment are selected according to the meridian diagnosis of TCM, which is primarily guided by where the pain is located and where it radiates to. Independent of investigating whether selecting acupuncture points according to TCM criteria is superior to the unspecific effect of random needling, the proposed study will investigate the inter-rater reliability of meridian diagnosis. Moreover, the subjective diagnosis of a TCM specialist with an assignment to corresponding meridians will be compared with the patient-created pain mapping with an assignment to local meridians. However, this study will not compare acupuncture with random acupuncture because this would tend to underestimate the effects of acupuncture [16]. As mentioned in the conclusion of the meta-analysis by Linde et al. [1], a non-inert effective therapy (i.e., MTT) will be compared with acupuncture and usual care.

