### Interventions

#### Acupuncture

The acupuncture treatment comprises a standardized combination of points plus additional individual points identified by location (meridian). Table 1 provides a detailed description of the acupuncture points used to allow replication of the intervention. All acupuncture points were selected based on TCM principles, the international literature, and the opinion of national and international experts. In line with the Standards for Reporting Interventions in Clinical Trials of Acupuncture criteria, the treatment was semi-standardized, fulfilling both the requirement of a basic individualized diagnosis and treatment and of a standardized acupuncture treatment for patients with comparable symptoms. In addition to these locations, needles will be inserted into 1–4 *ashi* points (i.e., points where the headache is most painful), if these points are clearly mentioned by the patient during the screening examination.

**Table 1 Tab1:** Acupuncture treatment

Point selection	Pain localization	Acupuncture points	Depth [cun]
Standard		*Baihui* (GV20)	0.5–0.8
		*Taiyang* (EX-HN5)	0.3–0.5
		*Fengchi* (GB20)	0.8–1.2
		*Hegu* (LI4)	0.5–1.0
*Yangming* meridian	Front head, forehead, brow edge	*Neiting* (ST44)	0.5–0.8
		*Yintang* (GV29)	0.3–0.5
*Shaoyang* meridian	Side head, temporal	*Zulinqi* (GB41)	0.3–0.5
		*Waiguan* (SJ5)	0.5–1.0
*Taiyang* meridian	Back head, occipital	*Kunlun* (BL60)	0.5–1.0
		*Houxi* (SI3)	0.5–1.0
*Jueyin* meridian	Top of the head	*Taichong* (LR3)	0.5–0.8
		*Neiguan* (PC6)	0.5–1.0
		*Sishencong* (EX-HN1)	0.5–0.8

The detailed localizations, acupuncture point names, and insertion depths follow the rules of TCM. All acupuncture points will be manually stimulated on needle insertion and before removal of the needle. The *deqi* sensation will be evoked. The needle retention time will be 30 min. Sterile disposable acupuncture needles will be used (25–40 mm × 0.25–0.3 mm; manufacturer: Suzhou Tianxie Acupuncture Instruments Co, or similar). Acupuncture will be used without additional methods, such as moxibustion, cupping or electrical, stimulation, which extend the technique or treatment. Acupuncture will be performed by an experienced acupuncturist with more than 5 years of clinical experience in acupuncture treatment.

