### Pain radiation

The precise headache pattern will be documented on a pain drawing created by the patient using an electronic pen on a tablet PC [28] running software SymptomMapper, which provides head outlines from four different views. Patients first choose descriptive terms for their pain and then color in all affected areas where they experience pain. Pain area and mean pain intensity will be calculated from these drawings.

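### A positive correlation between pain drawing and meridian diagnosis can show concordance of pain localisation, but not an improved TCM diagnosis as the Discussion states

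*Protocol article*

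**What the plan says.** The Discussion, in the paragraph on diagnostic tools after Figure 3, states that a positive correlation of the patient's pain drawing with "the independent TCM diagnosis, which focuses on the meridians affected, will bring an improved and objective TCM diagnosis to everyday clinical practice". It names no size of association and no agreement index.

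The Background describes where the two readings come from. Acupuncture points are chosen by a meridian diagnosis "which is primarily guided by where the pain is located and where it radiates to". The specialist's diagnosis, which the Background calls subjective, "will be compared with the patient-created pain mapping with an assignment to local meridians". Under Pain radiation, patients "color in all affected areas where they experience pain" on head outlines. Table 1, in the Acupuncture section, ties each of four meridians (Yangming, Shaoyang, Taiyang, Jueyin) to a head region.

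The Background keeps validity apart from this work: inter-rater reliability is studied "Independent of investigating whether selecting acupuncture points according to TCM criteria is superior to the unspecific effect of random needling", and no comparison with random acupuncture is made.

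The only numerical criterion nearby is in Research questions, where the null hypothesis for inter-rater reliability of meridian diagnosis is a kappa below 0.5. Statistical analysis sets a 0.05 significance level for all tests.

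**The concern.** The Discussion moves from an association to a claim of a better diagnosis, and three things break that step.

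- **Shared source.** Both readings largely encode one fact, namely where this patient's head hurts. Some positive association is expected from how the readings are made, whether or not meridian diagnosis adds anything beyond location.
- **Wrong quantity.** The meridian is one of four unordered labels. What matters is how often the two labels coincide beyond chance, and a positive correlation does not measure that.
- **Nothing to improve against.** No headache outcome, treatment response or reference standard enters the comparison, so it cannot show that one diagnosis is better than another.

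At stake is the interpretation of an exploratory aim. Agreement too weak to meet the protocol's own standard for meridian diagnosis could be reported as a diagnostic advance for everyday practice.

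**Working it through.** **Inputs.** The protocol gives no expected agreement for this comparison, so there is no figure of its own to reproduce. From the protocol come the four meridians (Table 1), n = 4 × 24 = 96 recruited or 4 × 20 = 80 analysed (Sample size estimation), and alpha 0.05, taken here as two-sided because sidedness is not stated. The category frequencies, the true kappa and one meridian per reading are assumptions. In the model, the specialist's label equals the drawing's label with probability κ and is otherwise drawn at random from the same frequencies, so κ is the true kappa.

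**Formulas, equal frequencies, n = 96.**

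- Chance agreement: pe = 4 × 0.25² = 0.25.
- Raw agreement: po = κ + (1 − κ) × 0.25. For κ = 0.2 this is 0.40; for κ = 0.3 it is 0.475.
- Standard error if κ = 0: √(pe + pe² − Σ ab(a + b)) / ((1 − pe)√n), where a and b are the two readings' frequencies for each category. This is √(0.25 + 0.0625 − 0.125) / (0.75 × 9.80) = 0.433 / 7.35 = 0.059. An estimate above about 1.96 × 0.059 = 0.115 is significant.
- Standard error otherwise: √(po(1 − po)/n) / (1 − pe). For κ = 0.2 this is √(0.40 × 0.60/96) / 0.75 = 0.067. For κ = 0.3 it is √(0.475 × 0.525/96) / 0.75 = 0.068.

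**Normal approximation.** For κ = 0.2, P(estimate > 0) = Φ(0.2/0.067) ≈ 0.999 and P(significant) = Φ((0.2 − 0.115)/0.067) ≈ 0.90. For κ = 0.3 the same steps give about 1.000 and 0.997.

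**Simulation (10,000 trials per row, same model).**

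| True kappa | Raw agreement | P(positive) | P(positive and significant) | P(estimate ≥ 0.5) |
|---|---|---|---|---|
| 0 | 25% | 0.494 | 0.027 | 0.000 |
| 0.1 | 32.5% | 0.941 | 0.397 | 0.000 |
| 0.2 | 40% | 0.999 | 0.894 | 0.000 |
| 0.3 | 47.5% | 1.000 | 0.997 | 0.002 |
| 0.4 | 55% | 1.000 | 1.000 | 0.064 |
| 0.5 | 62.5% | 1.000 | 1.000 | 0.473 |

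**Sensitivity.** With unequal frequencies (20/45/25/10%) and n = 80, κ = 0.2 gives 0.994 positive and 0.779 significant; κ = 0.3 gives 1.000 and 0.978.

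If an ordinary correlation coefficient is meant instead, Fisher's z at n = 96 (critical r = 0.201) gives lower figures:

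- true correlation 0.2: 0.975 positive, 0.498 significant;
- true correlation 0.3: 0.999 and 0.847;
- true correlation 0.4: 1.000 and 0.983.

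**Reading.** A kappa of 0.2 to 0.3 almost always satisfies a bar of 'positive' and almost never reaches an estimate of 0.5. Even a kappa above 0.5 would show only that the two readings place the pain alike.

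**The case against.** The strongest reply is that the sentence is an expectation in the Discussion. It appears in none of the hypotheses, outcomes or analyses, and the Background plans only a comparison. This stands: a reader might infer a formal decision rule that passes on a positive sign, and the documents contain no such rule. The choice of agreement statistic may also be settled in a fuller document. Even so, no statistic added there would turn agreement between two location readings into evidence of improvement.

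A reader might also infer that the result is positive whatever the data. That is too strong. Unrelated readings would give a positive sign about half the time, and a positive significant result about 2.5% of the time under the protocol's 0.05 level. Near-certainty needs real overlap, and how much overlap exists cannot be derived from the article. The Background says location guides the diagnosis primarily, not solely. It also describes tension-type headache as holocranial, so a drawing may cover several regions of Table 1 and need not fix one meridian.

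A further reply is that two methods must target the same thing for their concordance to mean anything, and that a patient-drawn map could make a subjective assignment more objective. This is fair. It supports reporting concordance and leaves 'improved' without support. Likewise, 'independent' can simply mean made separately, so the documents do not show that the word is false, only that it needs explaining.

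Finally, requiring a lower confidence limit above 0.5 would be a preference. The protocol states 0.5 for inter-rater reliability and does not tie it to this comparison.

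**Conclusion.** The point holds as an over-reaching inference about a planned exploratory comparison. Because both readings draw on the same patient's pain location and no outcome or reference standard is involved, a positive association is expected and cannot show an improved diagnosis. This part rests on the protocol's text alone.

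The size is illustrative. With four equally frequent meridians, one per reading, and n = 96, a true kappa of 0.2 to 0.3 is positive in about 99.9% of trials or more and significant in 89.4% to 99.7%. The range is somewhat lower with unequal frequencies or 80 patients, and lower again for an ordinary correlation coefficient. The primary and secondary efficacy conclusions and the sample size are untouched. The change is worth making because it is cheap, but it is not critical to the trial.

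**What to change.** In the Discussion paragraph after Figure 3, replace the inference with a statement along these lines: agreement between the meridian derived from the drawing and the meridian assigned by the specialist will be reported as kappa with a 95% confidence interval, read against the 0.5 benchmark already used for inter-rater reliability, and interpreted only as concordance of pain localisation, not as evidence of improved diagnosis or of treatment benefit. Remove 'improved', and say that 'independent' means the two readings are made separately. Since kappa needs one label per reading, the rule for drawings that cover several head regions should be cited with it.

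The same data serve. Near a kappa of 0.5 with n = 96 and equal frequencies, the interval would be about ±1.96 × √(0.625 × 0.375/96) / 0.75 = ±0.13, which is precise enough to be informative. The cost is a more modest exploratory conclusion and a benchmark that is harder to meet than a positive sign.

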### Limitations

The following four factors are potential confounders and concomitant variables:
Changes in individual behavior during the study. These could result from contact with the therapists or from directing attention to the symptoms. Behavioral changes will, as far as possible, be recorded in a behavior diary.Changes in other therapies, including self-treatment. These can include movement therapies or the intake of over-the-counter medication. Such changes will also be recorded in diaries if possible, to enable a correction of the results where necessary.Unspecific treatment effects. These can differ between the various study arms. For example, depending on treatment expectations, the unspecific effects of acupuncture can be stronger than those of physical training. In addition, there may be cultural influences and treatment expectations. These cannot be individually determined because of the excessive effort that would involve; however, potential effects will be addressed in the discussion of the results.Seasonal influences on pain. Such are likely to be present, but cannot be accounted for in the study. However, since the various study arms will be evaluated in parallel, potential effects would affect all study groups equally.

### Trial status

The trial commenced at the beginning of 2018. The approval of the ethics committee was given in June 2018. The recruitment of participants began in July 2018 and was completed in June 2019. The study will be finished in January 2020.

## Data Availability

Not applicable

## Abbreviations

ANOVA: Analysis of variance
GAD-7: Seven-item Generalized Anxiety Disorder Questionnaire
HRV: Heart rate variability
IHS: International Headache Society
MIDAS: Migraine Disability Assessment
MTT: Medical training therapy
PHQ-9: Nine-item Patient Health Questionnaire
PHQ-D: Patient Health Questionnaire, Depression
SF-12: 12-item Short Form Health Survey
SPIRIT: Standard Protocol Items: Recommendations for Intervention Trials
TCM: Traditional Chinese medicine
TMD: Temporomandibular disorder
